### Intervention description {11a}

Micropulse laser combined with ranibizumab group (group I): After three consecutive intravitreal injections of 0.5mg ranibizumab, patients are followed-up monthly in Beijing Hospital. If visual acuity decreases by greater than or equal to 5 ETDRS letters due to macular edema, then treat with micropulse laser (the treatment parameters we apply are 577nm micro-pulse laser, 200μm spot size, 5% duty cycle of 0.2 seconds, 400mW power, 7×7 grid, panmacular treatment) and sham intravitreal ranibizumab injection. And if visual acuity stays stable for at least two consecutive treatments (3 consecutive changes of no more than 5 letters), then discontinue micropulse laser treatment.

Ranibizumab monotherapy group (group II): After three consecutive intravitreal injections of 0.5mg ranibizumab, patients are followed-up monthly in Beijing Hospital. Sham micropulse laser and intravitreal ranibizumab injection will be performed as needed if visual acuity decreases by greater than or equal to 5 letters due to macular edema. If visual acuity stays stable for at least two consecutive treatments (3 consecutive changes of no more than 5 letters), discontinue intravitreal ranibizumab injection, then discontinue intravitreal ranibizumab injection.

### Criteria for discontinuing or modifying allocated interventions {11b}

Treatment of the study eyes will be based on the trial design and retreatment criteria. In case of severe vision loss (visual acuity decreased ≥15 letters compared with the last follow-up) due to exacerbation of DME, or severe adverse reactions, or participants’ request, subjects will be arranged to discontinue and leave the study and then continue with the next symptomatic treatment.

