#### Screening period: from day −14 to day −1

At screening (visit 1, between day −14 and day −1), after signing the informed consent (the model consent form is attached as a supplementary file), the patient is enrolled in the study and will undergo a series of examinations including ETDRS (Early Treatment Diabetic Retinopathy Study) visual acuity test, intraocular pressure measurement, slit-lamp, and indirect ophthalmoscopy, optical coherence tomography (OCT), optical coherence tomography angiography (OCTA), fundus fluorescein angiography (FFA), fundus color photography, vital signs, hematology, urinalysis, blood biochemistry, and glycosylated hemoglobin to assess eligibility for the study.

#### Treatment period: from day 1 to month 11

At baseline (visit 2, day 1), eligible patients will be randomized by 1:1 ratio into micropulse laser combined with ranibizumab group or ranibizumab monotherapy group. After baseline visit, all patients receive 3 consecutive monthly ranibizumab injections. Subjects will then return to the study site on day 90 (± 7 days) and according to the retreatment criteria, patients will either receive micropulse laser and sham intravitreal ranibizumab or sham micropulse laser and intravitreal ranibizumab. Thereafter, subjects will return to the study site every 30 days (± 7 days) for assessment (schedule shown in Fig. 2) and accept appropriate treatment according to the retreatment criteria.

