**Fig. 2 Fig2:**
[figure not shown]
Assessment protocol from V1 to V14. *BSL *Base line, *EOT *End of treatment, *EOS *End of study. (X): Give treatment as needed. b: Except at the time of screening, at month 6 and at month 12 / end of the study, if the investigator needed information to evaluate the retreatment. These assessments are optional for therapeutic needs. c: Evaluation of both eyes. d: At 2 (±1) days after each study treatment, the investigator should contact the patient for a possible report of adverse events

Group I (micropulse laser combined with ranibizumab group): 3 consecutive injections of intravitreal ranibizumab, followed by monthly observation, if:A.Visual acuity decreases by greater than or equal to 5 ETDRS letters due to macular edema, then treat with micropulse laser therapy and sham intravitreal ranibizumab injection.B.Visual acuity stays stable for at least two consecutive treatments (3 consecutive changes of no more than 5 letters), discontinue micropulse laser treatment.

Group II (ranibizumab monotherapy group): 3 consecutive injections of intravitreal ranibizumab, followed by monthly observation. According to the investigator’s judgment, if:A.Visual acuity decreases by greater than or equal to 5 ETDRS letters due to macular edema, then treat with sham micropulse laser and intravitreal ranibizumab injection.B.Visual acuity stays stable for at least two consecutive treatments (3 consecutive changes of no more than 5 letters), discontinue intravitreal ranibizumab injection.

#### Post-treatment follow-up period: from month 11 to month 12

For all patients, the last study assessment will occur at month 12 (1 month after the last possible micropulse laser or intravitreal ranibizumab injection in the study).

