## Assignment of interventions: Blinding

### Who will be blinded {17a}

Investigators responsible for follow-up evaluation, technicians who operate OCT, and data analysts are blinded. When intervention is required, the patient will either receive intravitreal injections plus sham micropulse laser treatment, or micropulse laser plus sham intravitreal injections. Therefore trial participants are blinded throughout the study. Only the investigators qualified for laser treatment and intravitreal injections are unblinded.

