### Procedure for unblinding if needed {17b}

In case of severe vision loss due to exacerbation of DME and requiring additional treatment or severe adverse reactions, subjects will be arranged to leave the study. The subjects who leave the group will be unblinded.

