### Methods in analysis to handle protocol non-adherence and any statistical methods to handle missing data {20c}

For missing values, the analysis will follow the LOCF (last observation carried forward) approach to obtain approximate results. If the patient dropped out, data of the last post-baseline observation during follow-up will take place of the missing data. If there were intermediate missing values (i.e., one missed visit during follow-up, then the patient resumed the visit), these values will be replaced with the mean value of the previous observation and the first subsequent observation.

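### The 15-letter exit for severe vision loss looks back only one visit, so a stepwise DME-related decline does not trigger it: a modest safety gap, mainly in Group I

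*Protocol article*

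**What the plan says.** All references are to the protocol article.

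- **Exit rule.** Criteria for discontinuing or modifying allocated interventions {11b} names three reasons to leave: "severe vision loss (visual acuity decreased ≥15 letters compared with the last follow-up") due to worsening DME, severe adverse reactions, and the participant's request. In each case "subjects will be arranged to discontinue and leave the study and then continue with the next symptomatic treatment".
- **Second statement of the exit.** Procedure for unblinding {17b} gives no letter count: "In case of severe vision loss due to exacerbation of DME and requiring additional treatment". Patients who leave are unblinded.
- **Visit spacing.** Trial design {8}, treatment period: after day 90, "subjects will return to the study site every 30 days (± 7 days) for assessment". The last assessment is at month 12.
- **Retreatment.** After three loading injections, a DME-related fall of at least 5 letters leads in Group I to this: "then treat with micropulse laser therapy and sham intravitreal ranibizumab injection". In Group II it leads to active ranibizumab plus sham laser.
- **Blinding.** Who will be blinded {17a}: "Therefore trial participants are blinded throughout the study".
- **Missing data.** Section {20c} foresees "one missed visit during follow-up, then the patient resumed the visit". For exits: "If the patient dropped out, data of the last post-baseline observation during follow-up will take place of the missing data".

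No section sets a limit against baseline, month 3 or best BCVA.

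**The concern.** A threshold measured from the previous visit limits the speed of loss and puts no limit on its total. With monthly visits, an eye can lose 15 letters or more while every single step stays below 15.

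This matters most in Group I. A declining Group I eye is retreated with laser and a sham injection, and the article gives no defined route back to ranibizumab within the study. Leaving is the way to other treatment, so the exit rule carries the protection. Group II has the same wording, but its retreatment contains active drug.

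The rule also depends on attendance. On the plain reading of the last follow-up as the last visit attended, two eyes with the same loss over the same two months can be handled differently only because one missed a visit.

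What is at stake is delayed rescue for a small number of patients.

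**Working it through.** The plan gives no figure to reproduce here. The check applies the stated rule to simple visit sequences and then estimates how often a cumulative limit would act.

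**Inputs from the article.** Exit: single-step fall of at least 15 letters ({11b}). Retreatment: fall of at least 5 letters ({8}, {11a}). Monthly visits from month 3 to month 12, so nine intervals ({8}). SD 6.53 and 36 patients per arm ({14}).

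**Step 1: two-visit sequences from month 3.**

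| Falls at months 4 and 5 | Largest single fall | Total | Exit under {11b}? |
|---|---|---|---|
| 8, 7 | 8 | 15 | No |
| 10, 10 | 10 | 20 | No |
| 14, 14 | 14 | 28 | No |
| 8, 7 with month 4 missed | 15 | 15 | Yes |

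Rows one and four are the same eye.

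**Step 2: interaction with retreatment.** A loss of 6 letters per visit meets the 5-letter retreatment rule each time, whether counted from the last visit or from month 3. By month 6 the total is 3 × 6 = 18 letters, with no exit. In Group I each response is laser plus sham.

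**Step 3: how often a limit of 15 letters from month 3 would act.** Assumption: the change from month 3 to month 12 is normal with SD 6.53. The article gives that SD for the sample size, not for this interval. The assumed mean change m is 0 or −5 letters.

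At month 12 alone, the share at least 15 letters down is Φ((−15 − m)/6.53):
- m = 0: Φ(−2.30) = 0.0108; × 36 = 0.4 patients.
- m = −5: Φ(−1.53) = 0.0628; × 36 = 2.3 patients.

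Over all nine visits, 1,000,000 eyes were simulated per case. An added exit is an eye at least 15 letters below month 3 at some visit with no single-visit fall of 15 or more. A confirmed exit needs this at two consecutive visits. The models are:
- random walk: step SD 6.53/3, drift m/9 per visit;
- visit noise: each reading has SD 6.53/√2 around a straight line to m;
- mixed: half the variance is a patient-specific slope and half is noise.

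| Model | m | Added exits of 36, unconfirmed | Added exits of 36, confirmed |
|---|---|---|---|
| Random walk | 0 | 0.5 | 0.2 |
| Visit noise | 0 | 1.6 | 0.2 |
| Mixed | 0 | 0.8 | 0.1 |
| Random walk | −5 | 2.7 | 1.5 |
| Visit noise | −5 | 4.8 | 0.9 |
| Mixed | −5 | 3.6 | 1.0 |

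In the visit-noise model no eye's true value falls by more than 5 letters, so every exit flagged there is a false alarm. Confirmation removes most of them: 1.6 falls to 0.2, and 4.8 to 0.9.

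Falls not due to DME would not count, so each figure is an upper one within its model.

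**The case against.** The strongest case against runs as follows.

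- **The rule is clear and equal in both arms, and the article is condensed.** The full protocol may say more: section {25} mentions drug combinations that the protocol prohibits, while {11d} prohibits none. That is possible, but {11b} states its criterion completely, with a number and a reference point. The point concerns that stated rule.
- **Stepwise decline is answered elsewhere.** A 5-letter fall triggers retreatment, with active drug in Group II. Patients can leave on request, severe adverse reactions are an exit, and adverse events are sought after each treatment ({22}). The wording in {17b} leaves some room for judgement. This stands in part and lowers the severity. In Group I, however, retreatment only repeats the laser. A patient can notice failing vision but does not know whether the injections are sham.
- **A month-3 reference can mislabel recurrence.** An eye that gained 15 letters in loading and then lost them is back at baseline, yet would count as severe loss. Noise adds to this: in the visit-noise model the flagged eyes' month-3 reading averaged about 7.7 letters (m = 0) or 5.8 letters (m = −5) above its true value. This stands, and it is why baseline is offered and why a month-3 fall needs confirmation.
- **Few patients can still benefit.** Trial status describes follow-up near its end, with new recruits only if patients are lost. This also stands.

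A reader might infer that patients could drift down 45 or 54 letters by month 12 (nine visits at 5 or 6 letters). The wording permits it arithmetically, but it is not a realistic course: entry BCVA is 24 to 78 letters, and the other exits exist. A reader might also infer a biased primary comparison. The documents do not support that: the exit wording is the same in both arms, and nothing in it shows a direction of bias.

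**Conclusion.** The point holds as a minor patient-safety gap. Followed exactly, {11b} lets a Group I eye lose 15 to 28 letters to DME over two monthly visits, on laser plus sham, without meeting the vision-loss exit. On the plain reading, it also makes the exit depend on attendance.

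The number of patients is small. With month 3 as reference and confirmation at the next visit, a cumulative limit would add about 0.1 to 0.2 exits of 36 per arm if the mean change is 0, and 0.9 to 1.5 if it is −5. These figures rest on transferring the planning SD of 6.53 to the month-3 to month-12 change, on the assumed means and on the three models. The unconfirmed upper figures of 1.6 and 4.8 should not be read as patients left unprotected, because they come from pure measurement noise. The step arithmetic needs none of these assumptions.

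**What to change.** In both arms, keep the present criterion and add a second one: a DME-related cumulative fall of at least 15 letters from a fixed, already recorded BCVA.

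- **Reference.** Baseline is the conservative choice and does not penalise loss of a loading gain. It acts later: an eye that gained 10 letters in loading must then lose 10 + 15 = 25. Month 3 gives earlier rescue. It is also a fair reference between arms, since both have had the same three injections and the envelopes are opened only at visit 5 ({16b}).
- **Confirmation.** If month 3 is used, require support from OCT, which Outcomes {12} schedules at every follow-up visit, and a repeat BCVA or the next visit. A prompt repeat avoids a further 30-day wait.
- **After exit.** Stop the allocated treatment, give symptomatic treatment, and still measure BCVA to month 12. Those values include the effect of rescue, so report the carried-forward result and the number of exits per arm beside them.
- **Scope.** Apply it to patients still in follow-up and to any new recruits.

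Cost: a short amendment with ethics approval and renewed consent ({25}). BCVA is already measured at every visit, so the only extra test is an occasional repeat reading. Outpatient visits for patients who drop out are already planned ({18b}). The main downside is roughly 0 to 1.5 more confirmed exits of 36 per arm on the stated assumptions, probably more in Group I. Each is unblinded under {17b}, and each is carried forward under {20c} unless BCVA is still measured.

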### Trial design {8}

This study is a prospective, single-center, randomized controlled, double-blinded non-inferiority clinical trial. A flow chart of the study design is shown in Fig. 1. Study subjects are 72 patients (more patients may be recruited) diagnosed with diabetic macular edema.

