#### Primary outcome measure

BCVA: Best corrected visual acuity is measured using standard ETDRS protocol at baseline and every follow-up visit. Changes in visual acuity will be compared between the two groups at a 12-month follow-up.

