### Plans to promote participant retention and complete follow-up {18b}

Investigators will contact patients 2 (± 1) days before each visit to promote patients’ retention and complete follow-ups. And we will also arrange follow-up visits at the outpatient clinic to support patients with subsequent treatment if they decide to drop out of the study.

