## Statistical methods

### Statistical methods for primary and secondary outcomes {20a}

The randomized set will consist of all randomized patients.

Full Analysis Set (FAS): Consists of all patients in the randomized set who are assigned to study treatment. They will be analyzed according to the treatment assigned to the subjects at randomization and the intention-to-treat principle.

Per Protocol Set (PPS): Consists of all patients in the full analysis set who complete the trial, had no significant protocol violations, and had no events that would confound the interpretation of the analysis. The analysis of the primary variable will be performed on the full analysis set.

For continuous and ordered categorical variables, analysis of variance (ANOVA) or analysis of covariance models which are both with baseline assessment as covariates were used to compare the changes between each treatment group and the baseline. Stratified and unstratified Cochran Mantel-Haenszel tests were also considered.

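### Leaving the study after severe vision loss means the month-12 outcome is never observed for patients selected by the primary variable

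*Protocol article*

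**What the plan says.** The section on discontinuing or modifying allocated interventions {11b} sets the trigger: "In case of severe vision loss (visual acuity decreased ≥15 letters compared with the last follow-up) due to exacerbation of DME". Severe adverse reactions and the patient's own request are the other two triggers. The consequence is the same for all three: "subjects will be arranged to discontinue and leave the study and then continue with the next symptomatic treatment". The unblinding section {17b} also has patients with severe vision loss or severe adverse reactions leave, and adds: "The subjects who leave the group will be unblinded".

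The primary outcome is tied to a fixed time: "Changes in visual acuity will be compared between the two groups at a 12-month follow-up". Change in CMT and the number of injections, both secondary, are compared at the same time. The trial is a "randomized controlled, double-blinded non-inferiority clinical trial".

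Statistical methods {20a} places the primary analysis on the full analysis set (FAS) and says of its patients: "They will be analyzed according to the treatment assigned to the subjects at randomization and the intention-to-treat principle". The per-protocol set (PPS) is narrower: "Consists of all patients in the full analysis set who complete the trial, had no significant protocol violations". For dropouts, section {20c} fills later values by last observation carried forward (LOCF).

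The only contact described after dropout is in the retention section {18b}, where the investigators will "arrange follow-up visits at the outpatient clinic to support patients with subsequent treatment if they decide to drop out of the study". That is care, not outcome collection.

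**The concern.** The exit rule acts on the primary variable. A 15-letter loss is three times the 5-letter difference used in the sample size section, and it ends observation for the patient who has it. The article commits to an intention-to-treat analysis at month 12, but the rule stops collecting the data which that analysis needs. No analysis plan can recover values that were never measured.

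Exits need not be balanced. After the three loading injections, retreatment in Group I is laser with a sham injection, and in Group II active ranibizumab with sham laser. Whether laser can hold vision without further injections is the trial's question. If it cannot in some patients, part of the shortfall would appear as extra exits in Group I.

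Three results are exposed: the FAS estimate, which rests on a value from around exit; the PPS estimate, which omits these patients; and the injection count, from which anything given after exit would be missing.

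**Working it through.** The plan gives no exit rate or size of loss among leavers, so there is no figure of its own to reproduce. The check is a reading of the text, followed by arithmetic on stated assumptions.

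**What happens to a leaver in each result**

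| Result | Treatment of a patient who leaves for DME worsening |
|---|---|
| FAS, BCVA (primary) | Kept in the randomised arm; month-12 value filled by LOCF |
| PPS, BCVA | Removed, because the trial was not completed |
| Month-12 CMT | Not measured |
| 12-month injection count | No provision to record injections after exit |

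**Inputs from the Sample size section:** SD 6.53 letters; 36 patients per arm; 5 letters, treated here as the non-inferiority margin. **Assumed:** exit proportions p1 (Group I) and p2 (Group II); a mean deficit D among leavers, the same in both arms; all other patients equal between arms.

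**All patients against completers.** Difference (Group I minus Group II) = -(p1 - p2) × D.
- 10% v 2%, D = 18: -0.08 × 18 = -1.44 letters, which is 1.44/5 = 29% of the margin.
- 15% v 5%, D = 18: -0.10 × 18 = -1.80 letters, 36% of the margin.
- PPS in both cases: 0, because the leavers are gone.

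**What LOCF does in the FAS** (10% v 2%, D = 18 at exit):
- Exit-visit BCVA recorded and carried forward: -1.44 letters, the same as the all-patient figure.
- Exit-visit value not used, preceding visit carried forward: that visit was at least 15 letters better, so the deficit is at most 18 - 15 = 3, and the difference is at most 0.08 × 3 = 0.24 letters against laser.
- Actual month-12 position if two thirds of the loss were regained under later treatment (assumed): D = 6, difference -0.08 × 6 = -0.48 letters.

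If that recovery occurred, carrying the exit value would overstate the deficit of laser by 1.44 - 0.48 = 0.96 letters. If there were no recovery and the preceding visit were carried, the deficit would be understated by at least 1.44 - 0.24 = 1.20 letters. The direction is therefore open.

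**Effect on the conclusion.** Simulation with 36 per arm, SD 6.53, margin 5, one-sided 0.025, leavers 15 letters lower, 4,000 trials per row:

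| Exits, Group I v II | Difference, all patients | Non-inferiority shown, all patients | Difference, PPS | Non-inferiority shown, PPS |
|---|---|---|---|---|
| 5% v 5% | 0.0 | 82.5% | 0.0 | 88.2% |
| 10% v 0% | -1.5 | 53.2% | 0.0 | 87.1% |
| 15% v 5% | -1.5 | 45.8% | 0.0 | 85.5% |
| 20% v 5% | -2.2 | 30.0% | 0.0 | 85.1% |
| 33% v 0% | -5.0 | 3.3% | 0.0 | 81.6% |

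The all-patient columns also describe the FAS with LOCF if the carried value has the assumed 15-letter deficit. The gap is thus between the all-patient analysis and the PPS; it is not an error of the FAS.

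**Injection count.** If leavers in both arms average the same number of injections after exit, each such injection shifts the arm difference by p1 - p2. At 10% v 2% that is 0.08 injections, omitted in favour of laser.

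**The case against.** A reader might infer that the failures disappear from the comparison that decides the trial and that the primary result is tilted toward non-inferiority. The documents do not support that. The primary analysis is on the FAS, which keeps these patients in their randomised arm, and the article gives the PPS no deciding role. The rule cannot fire without a BCVA measurement, and BCVA is taken at every follow-up visit, so LOCF would most naturally carry the poor exit value. On the illustrative figures the FAS then shows the full -1.44 letters. This part of the objection stands.

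Second, observed month-12 values may be kinder to laser than LOCF, because leavers go on to other treatment and the article prohibits no concomitant care. In the example the difference shrinks from -1.44 to -0.48 letters. This also stands: carrying the failure forward and observing the patient under later treatment answer different questions, and the choice should be explicit.

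Third, leavers are unblinded, and acuity testing depends on effort. Blinded assessors reduce this problem but do not remove it.

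Fourth, the rule needs a 15-letter loss between visits about 30 days apart, while retreatment starts at a 5-letter loss, so exits may be rare. The documents cannot settle this.

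What the objection does not answer is that the month-12 outcome is unobserved for these patients, that which value LOCF carries depends on whether the exit measurement enters the study record, and that the PPS omits them.

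**Conclusion.** The point holds in a limited form. Sections {11b} and {17b} tie stopping study treatment to leaving the study, so month-12 BCVA and CMT and later study-eye injections are not collected for patients selected by the primary variable. The FAS retains them with a carried-forward value that is not the month-12 outcome; the error may go either way and may count against laser. Bias toward similarity is shown only for the PPS, and only if exits are more frequent in Group I.

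The size rests on assumption: 1.4 to 1.8 letters between the all-patient and PPS differences for exits of 10% v 2% to 15% v 5% with an 18-letter deficit, both well inside 5 letters. The 33% v 0% row, which reaches the margin, is an extreme case. This is a worthwhile and inexpensive improvement, not a defect that invalidates the primary analysis. No judgement is made here on the clinical withdrawal criterion.

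**What to change.** Leave the clinical stopping criterion unchanged and separate stopping study treatment from leaving the study:

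- Unless consent is withdrawn, collect at least month-12 BCVA and OCT from these patients, measured by the assessors who are already blinded under section {17a}. Record every later study-eye treatment with its date, and include later injections in the 12-month count.
- Analyse the observed month-12 value in the FAS. Add a sensitivity analysis that carries the exit value forward, because later treatment can dilute the arm difference.
- Report exits for DME worsening by arm.
- Do not rest a non-inferiority conclusion on the PPS. Dropping the completion requirement alone may not restore these patients, since the PPS definition also excludes events that confound interpretation.

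Cost: one visit for what may be a few patients, at a hospital that already offers them outpatient follow-up, and an amendment. Section {25} requires a rewritten consent form, ethics approval and renewed signatures for any amendment. Patients unblinded at exit remain a weakness. The Trial status section expects last visits at the end of the year and allows for replacement recruitment, so the change helps only patients who have not yet passed month 12.
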